### Outcome measures

•
**Primary outcome:** Improvement of peripheral nerve regeneration of digital nerves in the hand measured using quantitative sensory tests (Semmes-Weinstein monofilaments and two-point discrimination tests measured and compared in the four presential assessments). The difference between the two treatment arms (group A × group B) measured through the sensory tests (SWM and 2PD) will be evaluated after randomization.•
**Secondary outcome:** Improvement of sensory functions and social participation of the individual submitted to neurorrhaphy of digital nerves of the hand measured through questionnaires (Cold Sensitivity Severity Scale described by
McCabe *et al.* (1991), and the Pain Disability Index questionnaire recommended by
Novak *et al.*, 2010).

**
*Semmes–Weinstein monofilament test (SWM).*
** The Semmes–Weinstein monofilament test is used to assess the perception of pressure thresholds, which reflect the reinnervation of peripheral targets. Using scored probes, the assessment of perception of touch/pressure is measured and recorded. This test is a prime marker of functional recovery and provides quantitative data that can be used to monitor the patient during the course of nerve regeneration (
Wang *et al.*, 2013).

Subjects were asked to place their hands over a table, and keep their eyes closed during this test. Each filament, starting with the smallest caliber, was tested over the pulp side of the affected finger. The filament was applied perpendicularly for 1 to 1.5 s in three trials. A positive response in at least 2 of the 3 trials marked the sensory threshold (
Gordon *et al.*, 2010). We used the test results for data analysis.

**
*Two-point discrimination test (2PD).*
** The two-point discrimination test, first described by WEBER in 1835 (
Dunlop *et al.*, 2019), is an established assessment tool for tactile gnosis (
Wang *et al.*, 2013). It is defined as the distance between compass points necessary for the patient to feel two contacts (
Rosén & Lundborg, 2000). Ideally, it is recorded as an absolute value compared to the corresponding portion of the contralateral, uninjured finger. Normal values in an undamaged strip of the finger vary from 2 to 6 mm (
Table 1).

**Table 1. T1:** Interpretation scale of the two-point discrimination test (reproduced from
Silva *et al.*, 2014).

Measurement	Interpretation
2 mm to 5mm	Normal
6 mm to 10 mm	Fair
11 mm to 15 mm	Poor
One point of perception	Protective
No point perceived	Anesthesia

Classification schemes for the two-point discrimination test such as the Medical Research Council (1954), modified by MACKINNON & DELLON (Modified Highet Classification), allow to divide into groups of value ranges according to the sensitive threshold of recovery (
Table 2).

**Table 2. T2:** Modified HIGHET’s classification (reproduced from
Dunlop *et al.*, 2019).

Sensory recovery	Highet	s2PD	m2PD	Recovery of sensibility
Failure	S0			No recovery of sensibility in the autonomous zone of the nerve
Poor	S1 S1+ S2 S2+ S3	>15 mm	>7 mm	Recovery of deep cutaneous pain sensibility Recovery of superficial pain and some touch sensibility Recovery of superficial pain sensibility As with S2, but with over response Recovery of pain and touch sensibility with no over response
Good	S3+	7–15 mm	4–7 mm	As in S3, but with good localisation of the stimulus but imperfect recovery of 2PD
Excellent	S4	2–6 mm	2–3 mm	Complete sensory recovery

s2PD = static two-point discrimination; m2PD = moving two-point discrimination.

**
*Cold Sensitivity Severity Scale (CSS).*
** The development of cold sensitivity is quite common after surgery and hand injury. After certain types of injuries, such as amputation and nerve damage, hypersensitivity can cause severe disability. The Cold Sensitivity Severity Scale developed by
McCabe *et al.* (1991) provides a reliable scale to measure cold sensitivity. The CSS scale includes four questions about events in the home that cause cold-related symptoms. To respond to each item, the patient is asked to place an X on a 100 mm line reflecting the severity of the symptom. The line had indicators at 25 mm intervals and underlying descriptors. The score for each item was then measured in millimeters from the beginning of the line, with the sum of the appropriate four-item subscale giving the cold-sensitivity severity score.

**
*Pain Disability Index.*
** The Pain Disability Index is a seven-item questionnaire designed to assess the extent to which pain interferes in the domains of daily life (family and household responsibilities, recreation, social activity, occupation, sexual behavior, self-care, and life support activity). Each item is rated on a scale from 0 (no disability) to 10 (total disability). The final score (ranging from 0 to 70) is calculated by adding the scores of each item, with a higher score indicating a higher level of disability due to pain (
Figure 2). The consistency, validity, and reliability of this questionnaire has been tested and proved to be useful in studies of nerve damage (
Novak *et al.*, 2010).

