**Figure 1. f1:**
[figure not shown]
Flow chart of the study based on CONSORT criteria.

Following surgery, both groups will additionally receive 1 hour of either electrical stimulation (group A) or sham (group B). In total, two silicone-carbon and gel electrodes (measuring 1 × 1 cm) will be used for all participants, with one placed exactly proximal and the other exactly distal to the surgical site. The two groups will receive the following therapeutic regimens:
•
*Group A: Surgery + PES.* The electrodes will produce a square-pulsed, biphasic, symmetrical current at a frequency of 20 Hz, pulse width of 0.4 ms, and amplitude at the motor threshold of the median nerve, for 1 hour directly after surgery (n = 16);•
*Group B: Surgery + sham PES.* The electrodes will produce a square-pulsed, biphasic, symmetric electric current at a frequency of 20 Hz, pulse width of 0.4 ms, and amplitude at the motor threshold of the median nerve, for 1 hour directly after surgery (the same as Group A) but the electrostimulator will be turned on only until the patient is aware of it, after which the amplitude will be set to zero (n = 16).

In the first post-operative review, the patient will be evaluated by the doctor at the outpatient clinic. A physiotherapist specialized in the area and blinded to the intervention will guide on the rehabilitation protocol that will be monitored remotely by electronic means available to the patient (WhatsApp, Skype, etc.). Patients will undergo a hand sensory re-education protocol based on the one proposed by
Dellon & Jabaley (1982) for a period of 3 months. This protocol involves exercises for discrimination of static and dynamic touch and objects of different shapes, sizes, and textures guided by the physiotherapist, and the patient is also stimulated to perform a home program exercises. This will involve a total of 20 remote monitored sessions lasting about 30 minutes each, carried out, on average, twice per week. No videos or photos of the patients will be acquired to guarantee the patient’s privacy and data confidentiality.

Patients will be evaluated in person after every 10 treatment sessions by the main author of the study, who is responsible for the surgical and postoperative follow-up of the study participants but blinded to group allocation.

Participants must complete a total of 4 face-to-face assessments to document the results:

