‐1 pre-intervention/electrical stimulation‐1-week post-electrical stimulation‐1 after 10 rehabilitation sessions‐1 after all 20 rehabilitations sessions

The research will be completed within 1 year.

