### Statistical analysis

All statistical tests will be performed using
SPSS (V25.0, IBM Corporation, New York, USA). The data will be evaluated in a paired and non-paired way. For paired evaluations (intra-group comparisons), repeated measures ANOVA or the Friedman test will be used, followed by the Student–Newman–Keuls post-test. For non-paired assessments (comparisons between groups), analysis of variance of a measure (one-way ANOVA or the Kruskal–Wallis test) will be used, followed by the Student–Newman–Keuls post-test. The choice of tests will depend on the normality or the nature of the data.

For statistical analysis, the 95% confidence interval will be considered, with an alpha of 5% (P < 0.05) and power of 80%. Descriptive analysis will be done through the averages or medians associated with the applicable dispersion measures (standard deviation or quartiles 25/75). Both the measurements of the variables in each study and the statistical analysis will be performed blindly.

The independent variable for both groups will be the use of electric currents. The dependent variables will be derived from the pre- and post-treatment assessments (Semmes-Weinstein monofilaments, two-point discrimination, Cold Sensitivity Severity Scale and Pain Disability Index).

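### Two primary sensory tests with no lead test or primary time point, arms compared at 5% each: on the natural reading, the false positive risk is about 20 to 24%, not 5%

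*Protocol article*

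**What the plan says.** Under Outcome measures, the primary outcome is nerve regeneration measured by the Semmes–Weinstein monofilament test (SWM) and two-point discrimination (2PD), "Semmes-Weinstein monofilaments and two-point discrimination tests measured and compared in the four presential assessments". The next sentence says that the difference between arms, "measured through the sensory tests (SWM and 2PD) will be evaluated after randomization". It names no visit.

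The Intervention section sets the schedule: "Participants must complete a total of 4 face-to-face assessments to document the results". The first is "1 pre-intervention/electrical stimulation". The other three follow stimulation: at one week, after 10 rehabilitation sessions, and "after all 20 rehabilitations sessions".

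Under Statistical analysis, repeated measures ANOVA or the Friedman test is assigned to comparisons within a group. For comparisons between groups, "analysis of variance of a measure (one-way ANOVA or the Kruskal–Wallis test) will be used", followed by Student–Newman–Keuls. The level is "alpha of 5% (P < 0.05) and power of 80" percent. Nothing ranks the two instruments or the visits.

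The section on sample size and allocation rests on a different test: a repeated measures ANOVA interaction with two groups and three measures, at a single 5% alpha.

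**The concern.** A 5% error rate for the primary claim requires either one primary test or a rule that shares 5% among several. The article gives neither. Its between-group test ignores time, so following the text means one A-versus-B test for each instrument at each visit. Student–Newman–Keuls sorts out differences among groups within one ANOVA. With two groups there is only one such difference, so it adds nothing across visits or instruments.

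A significant result on either instrument at any post-intervention visit could then be presented as the primary finding. The conclusion would depend on which visit and which instrument were put forward, in a trial of 32 patients whose result is meant to inform the planning of a stimulation device.

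**Working it through.** **Inputs from the protocol article.** Two primary instruments; four assessments, three of them after stimulation; alpha 0.05; 16 per arm; and, from the sample size paragraph, effect size 0.26, three measures, correlation between repeated measures 0.5 and non-sphericity correction 1.

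**Assumed, because the article does not give it.** A correlation between SWM and 2PD of 0.3 to 0.7. The 0.5 between visits is a sizing input, not reported data on SWM or 2PD, so it was varied as well.

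**1. The plan's own figure.** For the group-by-time interaction with N = 26, m = 3 measures and k = 2 groups:
- noncentrality = f²·N·m/(1 − ρ) = 0.26² × 26 × 3/0.5 = 10.5
- degrees of freedom = (k − 1)(m − 1) = 2 and (N − k)(m − 1) = 48
- power at alpha 0.05 = 81.1%

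The stated 26 is therefore reproduced. Adding 20% gives 31.2, taken as 32. This is the size for one interaction test at 5%.

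**2. Number of comparisons.** 2 instruments × 3 post-intervention visits = 6.

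**3. Error if independent.** 1 − 0.95⁶ = 26.5%.

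**4. Error with correlation.** Null trials were simulated (40,000 per setting, 16 per arm, two-sample t tests, which equal one-way ANOVA for two groups, and equal correlation between visits). The table gives the probability of at least one P < 0.05 among the six:

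| Visit correlation | SWM–2PD 0.3 | 0.5 | 0.7 |
|---|---|---|---|
| 0.5 | 22.9% | 22.0% | 20.6% |
| 0.7 | 20.7% | 19.4% | 17.8% |
| 0.9 | 15.6% | 15.4% | 14.0% |

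A separate run at visit correlation 0.5 gave 23.6%, 22.1% and 21.0%. Together the two runs give about 20 to 24%.

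**5. If the sizing interaction were the primary test of each instrument.** There would be two tests at 5%: 1 − 0.95² = 9.75% if independent, and never more than 10%.

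**6. One time point, one lead test or Holm over two.** At most 5%.

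**The case against.** The strongest objection is that the text does not literally prescribe these tests. The phrase about four assessments may describe the within-group course, which has its own analysis, and the sentence on the arm difference names no visits. The 5% is given as a general level. The article does not say that each comparison will be declared positive without adjustment, and a multiplicity rule could sit in an analysis plan that is not shown. This stands in part: six separate tests are the natural reading, not an explicit statement. But the article itself fixes two primary instruments without a time point and a between-group test without a time factor. The point rests on those statements.

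A second objection is that the trial was sized for one interaction test per instrument, which leaves no visit to choose. On that reading the error is about 10% at most, still above 5%. However, the Statistical analysis section does not name that test as the between-group analysis.

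A reader might also infer eight comparisons, because four assessments are mentioned, with an error of 25 to 28% at visit correlation 0.5 and 33.7% if independent. The documents do not support that count for efficacy. The arm difference is to be evaluated after randomization, nothing presents a pre-intervention difference as a result, and such a difference cannot be a treatment effect.

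**Conclusion.** The point holds. The primary outcome leaves open which instrument and which visit decide the trial, and nothing stated holds the overall error at 5%. For six post-intervention comparisons the error is about 20 to 24% at visit correlation 0.5, 14 to 16% at 0.9, and 26.5% under independence. On the single-interaction reading it is up to about 10%.

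These figures rest on separate between-arm tests at each post-intervention visit and on an assumed SWM–2PD correlation of 0.3 to 0.7. An unqualified one-in-four would go too far, because the figure falls as the visits become more correlated and the article gives no observed correlation for either instrument. Every value in the range is nonetheless well above the nominal 5%.

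**What to change.** In Outcome measures and Statistical analysis, name the final assessment, after all 20 sessions, as the only primary time point. Then do one of the following:
- Test SWM first at 5%, and 2PD at 5% only if SWM succeeds. The article describes SWM as a leading marker of functional recovery, but it also calls 2PD an established tool and does not rank the two. The order is therefore the investigators' choice, to be made before unblinded data are seen.
- Keep both as primary and apply Holm to the two P values.

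Report the earlier post-intervention visits as supportive, with estimates and confidence intervals. Do not test the pre-intervention visit for efficacy.

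The cost is wording only: no patient, visit or measurement is added. The fixed sequence costs the first test nothing. Holm costs some power. For an assumed effect of 1.10 SD (not a figure from the documents) and 13 per arm, the noncentrality is 1.10 × √(13/2) = 2.80 on 24 degrees of freedom, and power falls from 0.77 at the 0.05 level to 0.66 at the 0.025 level. No recovery of that loss through baseline adjustment should be claimed. It would need a baseline-to-final correlation of about 0.5, and the baseline is measured after nerve transection, where the documents give no support for such a value.

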**Figure 2. f2:**
[figure not shown]
Pain Disability Index questionnaire. (Reproduced from
Wang *et al.*, 2013).

### Sample size and patient allocation

Patient allocation and statistical analysis will be done by a researcher ([name]) who will be blinded to the procedures and groups. A simple randomization will be performed using sealed and opaque envelopes. There will be 16 patients per group (groups A and B), totaling 32 patients. The sample size is based on the study by
Gordon *et al.* (2010), as this is the only randomized clinical trial in the literature. We estimated the sample considering a repeated measures analysis of variance (ANOVA) test with interaction between and inter factors, with an effect size of 0.26 (according to
Gordon *et al.*, 2010), alpha-type error of 5%, power of 80%, two groups, three measures, with correction between factors of repeated measures of 0.5, and correction of non-sphericity of 1. These parameters resulted in 26 individuals in the total sample (13 per group), which were increased by 20% to compensate for possible losses, resulting in a final sample of 32 patients (16 per group). The selection of the sample to compose the two groups will be carried out by an experienced (>10 years) hand surgeon, through the clinical examination and application of evaluation tools (Semmes-Weinstein monofilaments, two-point discrimination tests, Cold Sensitivity Severity Scale and the Pain Disability Index).

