Brushart *et al.*, 2002). The latter allowed more precise and faster reinnervation; increased the expression of brain-derived neurotrophic factor (BDNF), tyrosine receptor kinase B (TrKB), Tα1-tubulin, and growth associated protein 43 (GAP-43), and other genes/proteins associated with regeneration; and reduced expression of neurofilaments (a phenomenon associated with regeneration). This model has been the only one to be translated to humans, so far.
Gordon *et al.* (2010) evaluated the same electrical stimulation protocol in patients with denervation of the muscles of the thenar region due to carpal tunnel syndrome. They observed that the treatment accelerated axonal regeneration without affecting function. Intraoperative electrostimulation differs from others, in addition to the form of stimulation, for the brief time it is used (approximately 1–2 hours of stimulation following injury).

**
*Thin-film wireless implantable nerve stimulators.*
** Using widely established technology, wireless devices dedicated to peripheral nerve stimulation have been used to improve functional recovery in a rodent model, without the additional time needed to provide direct stimulation during the surgical procedure (
Ray *et al.*, 2017). This strategy has not yet had practical application in humans.

**
*Surface electrodes.*
** The use of transcutaneous surface electrodes is a non-invasive option that can be used for a longer period, especially when associated with biphasic electrical currents. Its handling is practical and simple, avoiding the reactions provoked by implant surgery or percutaneous stimulation.

Previous studies have evaluated the influence of peripheral electrical stimulation (PES) through surface electrodes on the regeneration of tissues such as tendons (
Burssens *et al.*, 2003,
2005), skin (
Kaada & Emru, 1988;
Kjartansson *et al.*, 1988;
Khalil & Merhi, 2000;
Liebano *et al.*, 2003), and bone (
Kahn, 1982), with varying results. This modality is associated with effects such as increased blood flow (from
Sandberg *et al.*, 2007;
de Vries *et al.*, 2007) and collagen synthesis (
Burssens *et al.*, 2005). However, electrical currents with amplitudes above 1 mA are needed, which may be related to decreased concentrations of adenosine triphosphate (ATP) (
Cheng *et al.*, 1982) and, consequently, inhibition of peripheral nerve regeneration.

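### The 80% power is shown only for a group-by-time interaction test that the analysis section does not plan; the power of the planned between-arm test is not established

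*Protocol article*

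**What the plan says.** Sample size and patient allocation (protocol article) bases the calculation on a "repeated measures analysis of variance (ANOVA) test with interaction between and inter factors, with an effect size of 0.26", with "alpha-type error of 5%, power of 80%, two groups, three measures", a correlation of 0.5 between repeated measures and a non-sphericity correction of 1. The result is 26 patients, 13 per arm. Adding 20% for losses gives 32, or 16 per arm.

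Statistical analysis assigns the tests differently:
- Within arms: "For paired evaluations (intra-group comparisons), repeated measures ANOVA or the Friedman test will be used".
- Between arms: "For non-paired assessments (comparisons between groups), analysis of variance of a measure", specified as one-way ANOVA or Kruskal–Wallis.

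No test in that section combines group and time. The section then restates an alpha of 5% and a power of 80%.

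Outcome measures defines the primary comparison as group A against group B on the monofilament and two-point discrimination tests. These are measured at four visits, and no single visit is named. The Intervention section agrees on the number of visits: "Participants must complete a total of 4 face-to-face assessments to document the results" (one before stimulation and three after). The sample size calculation uses three.

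**The concern.** A power statement belongs to one test and one alternative. Here the test that was powered asks whether the two arms change differently over time, and that test is not among those planned. The planned tests do something else. The within-arm tests ask whether each arm changes, which says nothing about the difference between arms. The one-way test compares arms at a visit that is not specified, and its power depends on a quantity that the calculation does not supply.

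Two things are at stake. First, a reader will take 80% as the power of the between-arm comparison, which the document does not show. Second, the only longitudinal tests are within-arm, so the plan invites the argument that a significant change in A with a non-significant change in B shows benefit. If recovery were identical in both arms and each within-arm test had power p, that pattern would arise with probability p(1 − p). Its maximum is 0.5 × 0.5 = 25%.

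**Working it through.** **Inputs** (all from Sample size and patient allocation): effect size 0.26, two groups, m = 3 measures, correlation ρ = 0.5, non-sphericity 1, alpha 0.05. The document does not say what kind of effect size 0.26 is. It is taken here as Cohen's f, which the exact reproduction below supports.

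**Step 1: reproduce the 26.** For the within-between interaction, the noncentrality is λ = f²·N·m/(1 − ρ), with df (m − 1) and (N − 2)(m − 1).
- N = 24: λ = 0.0676 × 24 × 3/0.5 = 9.73, df 2 and 44, power 77.5%.
- N = 26: λ = 0.0676 × 26 × 3/0.5 = 10.55, df 2 and 48, power 81.1%.

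The smallest even N reaching 80% is 26, as stated. At N = 32 the power is 89.2%. The same f in a one-way ANOVA would need N = 120, so the 26 belongs to the interaction test.

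**Step 2: translate f = 0.26 into a difference at the last visit.** Let the arm difference follow a pattern over the three measures, scaled so that its largest value is 1, and let c be the pattern minus its mean. Then f = (D/2)·√mean(c²), so D = 0.52/√mean(c²) in SD units, where D is the largest difference. The time patterns are assumptions, because the document gives none. All start with equal arms.
- 0, 0, 1 or 0, 1, 1: mean(c²) = 2/9, D = 0.52/0.471 = 1.10.
- 0, 0.75, 1: D = 1.22.
- 0, 0.5, 1: mean(c²) = 1/6, D = 0.52/0.408 = 1.27.
- 0, 1, 0.5: D = 1.27 at the middle measure, so 0.64 at the last.
- 0, 1, 0: nothing at the last.

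**Step 3: power of the planned one-way ANOVA at the last visit.** λ = (d/2)²·N, df 1 and N − 2, where d is the last-visit difference. For example, d = 1.10 at N = 26 gives λ = 0.304 × 26 = 7.91.

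| Alternative | Last-visit difference | N = 26 | N = 32 |
|---|---|---|---|
| Late, or reached early and sustained | 1.10 SD | 77% | 86% |
| 0, 0.75, 1 | 1.22 SD | 85% | 92% |
| Linear divergence | 1.27 SD | 88% | 94% |
| Early, half faded | 0.64 SD | 34% | 41% |
| Early, fully faded | 0 | 5% | 5% |
| 0.26 read as the one-way f (d = 2 × 0.26) | 0.52 SD | 25% | 30% |

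**Step 4: what a simple final-visit comparison detects.** Solving the Step 3 formula for 80% power gives f = 0.573, or d = 1.15 SD, at N = 26, and f = 0.512, or d = 1.02 SD, at N = 32.

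**Step 5: three measures or four.** With m = 4 and the same f, ρ and alpha, the interaction power is 87.9% at N = 26 and 94.2% at N = 32.

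**The case against.** The best defence is that a between-arm test is planned and is valid in a randomised trial: comparing arms after treatment needs no interaction term. If the effect size behind the 26 is taken at face value and the arm difference builds up and persists, that test performs well. Of the 13- and 16-per-arm results for building effects, only 1.10 SD at 13 per arm falls below 80%. This stands. A reader might infer that no planned test has 80% power, but the figures do not support that. The 25–30% result requires reading an interaction effect size as a one-way effect size, which is a different alternative from the one that produced the 26.

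Two further inferences also go too far. A reader might think that using three measures when four are planned costs power. At the same f, four measures raise the interaction power, so this is an inconsistency to reconcile and not a shortfall. A reader might also think 0.26 is unsuitable because the protocol says of the cited trial: "They observed that the treatment accelerated axonal regeneration without affecting function". But the document does not say which outcome of that trial gave 0.26. It labels its own primary outcome as nerve regeneration and cites the same trial for its monofilament procedure. Whether 0.26 is suitable cannot be judged from the document.

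The defence does not remove the mismatch. Two sections of the same document name different tests, and the analysis section attaches 80% to tests for which it was not calculated. This is a contradiction in the text, not a detail left to an analysis plan.

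**Conclusion.** The point holds in this form: the 80% and the 26 are correct for a group-by-time interaction test (81.1%), that test is not in the planned analysis, and the power of the planned between-arm test is not established. Under the interaction effect that gives 26, that power is 77–88% at 13 per arm and 86–94% at 16 if the difference builds to the last visit. It falls to 34–41% if the effect half fades, and to 5% if it disappears by then. Which case applies depends on a time course that the protocol does not state.

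The within-arm tests cannot fill the gap: significance in A without significance in B must not be read as a treatment effect. The 25% given for that pattern is a ceiling, reached only if each within-arm test has exactly 50% power.

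The calculations assume that 0.26 is Cohen's f, that the data are roughly normal with equal variance, and that one outcome is tested at alpha 0.05. The rank-based alternatives in the plan were not evaluated.

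**What to change.** In Statistical analysis, name one model with group, time and group-by-time as the primary analysis. Report the between-arm contrast at the final assessment with its 95% confidence interval. State that the within-arm tests are descriptive and will not be used to infer a treatment effect.

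In Sample size and patient allocation, state the power for that analysis, using the number of assessments actually analysed and reconciling three with four. Keep the power of the overall interaction test separate from that of the final-visit contrast, because they differ. State that a simple final-visit comparison has 80% power for a difference of about 1.02 SD with 16 per arm, or 1.15 SD with 13 per arm after losses. Remove the unqualified 80% from the analysis section or tie it to the named test.

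The cost is wording in two sections and no extra patients. The price is candour: the detectable difference, about one SD or more, is shown to be large.
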